#### Informed consent

Once screened, the Clinical Coordinator will provide the informed consent in the local language at the participating site to eligible subjects who are willing to be enrolled into the study. After reading the informed consent to the subject and answering any questions she may have, the Clinical Coordinator will ask her to sign the informed consent. If the subject is illiterate, confirmation will be obtained as a thumbprint in the presence of a witness. Women will be assured that refusal to participate in the study will in no way affect further treatment or care at the clinic.

#### Enrollment and baseline data collection

Once screened, the Clinical Coordinator will enroll eligible subjects who provide informed consent. The Clinical Coordinator will complete the enrollment form, and will obtain a blood sample (about 8 ml) from the subject for baseline measures of RBC, hemoglobin, B12, and serum/RBC folate.

Blood samples will be analyzed at a maximum of 2 weeks. Enrollment of subjects with normal B12 levels will be confirmed. Subjects found to be B12 deficient will be referred to a hematologist for treatment, and will be excluded from participation.

The Clinical Coordinator will randomize each confirmed subject into the 0.4 and the 4 mg folic acid groups (see section 3.6) and will dispense the folic acid pillbox with the relevant pillbox ID number. Study pills will be sent to randomized subjects by mail in most cases; subjects with unreliable addresses or who frequently attend the clinic for care receive their pills at the clinic. When delivered by mail, the clinical coordinator will contact the subject by phone to confirm their receipt of the pillbox.

#### Randomization procedures

Study subjects will be randomized to either 4mg or 0.4mg of folic acid. The study will be double-blinded; subjects, investigators and research staff will be blinded to the randomization assignments.

The Data Center will prepare the randomization sequence for the study using permuted blocks of random size. Randomization occurs at the subject level and is stratified by study site to ensure a balanced site representation in both treatment groups. The randomization will not be stratified according to risk group (mother with oral cleft or mother of child with oral cleft) or other factors due to the large sample size. As shown in
[121], stratification becomes irrelevant after the sample rises above 200 subjects. Since randomization occurs at the mother’s level, the sample allocation should be very well balanced with respect to the risk group and other factors.

The randomization sequence will link the treatment assignment (0.4mg or 4mg) to a sequential list of serial numbers to be used for the study pill boxes. The Data Center will generate the randomization sequence. The Data Center will supervise the labeling of the boxes with the serial number. In addition, the boxes will be numbered in order of dispensing (1, 2, 3, etc.3). The serial and dispensing order numbers will be recorded on the study visit/follow-up form to track dispensing.

The random assignment will be accomplished by assigning the next serial number in the randomization list as the enrollment of each new subject is confirmed. Once confirmed, the study subject ID is recorded in a computerized randomization log (that will include randomization order, serial number of assigned pill box and the study subject ID). The Clinical Coordinators will affix the study subject ID labels to the boxes of each subject with the serial number assigned to her.

The Data Center will maintain the randomization sequence at RTI headquarters in NC. Revealing the individual assignment will be highly restricted and will only be done if deemed clinically necessary. Only a physician attending to the study subject may request revealing the treatment assignment for a clinical purpose. The Co-Principal Investigator will review this request and evaluate the necessity of revealing the treatment assignment for the given purpose. The individual assignment will be revealed only after the Co-Principal Investigator approves the request. The Manual of Operations details the procedures for requesting the individual assignment from the Data Center.

#### Study treatments

The study drugs are folic acid in concentrations of 4mg (high dose) and 0.4mg (low dose). The study drugs are supplied in tablet form, manufactured by ATIVUS Pharmaceutical Industries in Sao Paulo, Brazil. Quality control assessments of samples of production batches will be performed for all manufacturers in an independent quality control lab in the United States (Celsis Laboratory Group, Saint Louis, US). All pills, regardless of their folic acid concentration, will be identical in size, shape, and color and will be provided in identical packaging. Patients enrolled in the study will be instructed to ingest 1 tablet daily from enrollment until 3 months gestation.

The manufacturers will package the folic acid pills in boxes containing 5 blister packs of 14 pills each (2 rows of 7 pills), for a total of 70 pills per box. Each box will contain an information sheet that will include all recommendations of the country’s drug monitoring agencies (ANVISA for Brazil) regarding information about the drug, yet will not reveal in any way the actual folic acid content. The manufacturer will also label each of the pill boxes with the following information, in addition to any other item that is recommended by the monitoring agency:

Manufacturing and expiration dates (including only the month and the year of production which will be common for the two doses of folic acid)

Description of the drug (folic acid)

Identification of the manufacturer

Statement about the use of the drug (“this product is solely intended for research use and shall not be commercialized”)

Patient instructions for taking pills (or if a daily dose is missed)

Clearance number of monitoring agency

Clinic’s logo

The manufacturers will also label the blister packs with a production lot number. Each production run of pills will use several lot numbers for each dose. The lot numbers pertaining to each dose will be sent from the manufacturer directly to RTI after each production run.

After each production, RTI staff will supervise labeling the pillboxes with a serial number (##### - ##, a seven digit number with 5 digit base number and 2 check digits). A local staff independent of the study may be used to label the pill boxes.

There will not be any information on the pill box or blister pack that may indicate to the subject the folic acid content of the pills.

A sample of pills from the boxes will be selected from each production lot to be sent out for independent assay of folate content to assure manufacturing compliance.

#### Follow-up of study subjects

Subjects will be followed up every 2 months (approximately 8 weeks) post enrollment to deliver the study pills and evaluate their health status, pregnancy occurrence, and compliance with study pills. The study pills will be delivered to subjects through express mail when no in-person follow-ups are scheduled; subjects will be contacted by phone in this case to complete the follow-up data form and ensure that pills have been received. Periodic in-person follow-ups will be conducted every six months if subjects are available; otherwise a phone and mail follow-up will be conducted. During each follow-up, the subjects will be advised of the date and time of their next appointment. Within two weeks prior to each in-person follow-up, the Clinical Coordinator will contact the subject by mail or telephone to remind her of the follow-up date.

If subjects report menstruation delays of 14 days or more during the follow-up and pregnancy has not been confirmed, the study staff will advise the subject to take a pregnancy test either at the study clinic, at an outside clinic, or at home if subject prefers (subjects will be reimbursed for pregnancy tests outside of the study clinic).

Subjects who are confirmed to be pregnant will be advised as when to stop taking the study pill so that the intervention is limited to the first trimester of pregnancy. Gestational age will be calculated based on the last menstrual period. Pregnant subjects will be referred to prenatal care as soon as pregnancy is confirmed.

Pregnant subjects will be monitored by their local prenatal care providers. Participating subjects might receive care from various prenatal care providers during the pregnancy period and may not have a single prenatal care provider. Most women usually seek prenatal care at public health clinics, where they may get assigned a different provider at each visit. Thus it might be hard to maintain contact between the Clinical Coordinator and the prenatal care providers of the subjects. The Clinical Coordinator will attempt to initiate and maintain contact with identified prenatal care providers to follow up on pregnancy progress. The Clinical Coordinator will also maintain periodic direct contact through phone with the subject to check on her pregnancy progress.

Upon delivery, the Clinical Coordinator will follow with the subject and her physician to check on the occurrence of NSCL/P and other birth defects in the infant. Research staff may also access prenatal care records of subjects, pending approval of subject prenatal care providers, to abstract significant health and care events that occurred during pregnancy and that required physician care.

The Clinical Coordinator or Co-Prinicipal Investigator will also evaluate in person the infant for the presence clefting and other anomalies either through an appointment at the clinic or at subject’s home as convenient to the subject. When a birth defect is identified, research team members will carry out a complete physical exam and confirm all oral cleft diagnoses. The Co-Principal Investigator may also evaluate the infant along with the Clinical Coordinator or independently.

Gestational loss will be reviewed by one of the research team members (Clinical Coordinator, Co-Principal Investigator, and/or geneticists of the clinic). When available, miscarriage material will be examined. This examination will may include macroscopic analysis (presence or absence of NSCL/P; other apparent malformations), photographic documentation, and cytogenetic analysis in the event of malformations depending on the capacity of the clinic site in doing these investigations.

After completion of a pregnancy outcome, subjects will be asked about their willingness to resume participation in the study at an appropriate time following the end of pregnancy. Subjects who are willing to resume participation will be assigned to the same treatment group as their previous randomization assignment, and the standard enrollment procedures will be followed.

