## Abstract

**Background:**

Oral clefts are one of the most common birth defects with significant medical, psychosocial, and economic ramifications. Oral clefts have a complex etiology with genetic and environmental risk factors. There are suggestive results for decreased risks of cleft occurrence and recurrence with folic acid supplements taken at preconception and during pregnancy with a stronger evidence for higher than lower doses in preventing recurrence. Yet previous studies have suffered from considerable design limitations particularly non-randomization into treatment. There is also well-documented effectiveness for folic acid in preventing neural tube defect occurrence at 0.4 mg and recurrence with 4 mg. Given the substantial burden of clefting on the individual and the family and the supportive data for the effectiveness of folic acid supplementation as well as its low cost, a randomized clinical trial of the effectiveness of high versus low dose folic acid for prevention of cleft recurrence is warranted.

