[115] reported a 35% reduction in recurrence of cleft lip and/or cleft palate (p=0.2), but a 65% reduction in CL/P recurrence (p=0.06). Tolarova
[116] reported an 84% reduction in recurrence of CL/P in a group of 80 women who received a multivitamin and 10 mg of folic acid during three months before conception and throughout the first three months of pregnancy (p=0.02), compared to a control group of 202 women. Using data on a larger sample that included women with CL/P (40% of intervened sample) and mothers of a child with CL/P, and the same intervention as Tolarova
[116] and Tolarova and Harris
[117] reported a 66% reduction in recurrence of CL/P (p=0.03) The average reduction effect when combining the unique data samples of these studies
[8,115,117], is 54.1% (47% when Conway (1958) is excluded), and 66.5% for CL/P recurrence combining Tolarova and Harris
[117] and the CL/P sample of Briggs
[115]. These calculations are inappropriate from a confirmatory side given the array of interventions and populations used, but from an exploratory perspective, may be helpful for gauging expected treatment effects of folic acid to form hypotheses in clinical trials. Our study hypothesis of 50% reduction is based on this result, the case–control observational study results, many of which also suggested similar effects, and the result of MRC study which showed a 78% in recurrence of NTDs
[118].

The results of these studies are suggestive of potential preventive effects of high dose folic acid on cleft recurrence. The data from the Hungarian trials
[79,110] also support the notion of lack of preventive effects of low doses of folic acid on occurrence of oral clefts. The NTD model showing preventive effects of high and low dose folic acid on recurrence and occurrence respectively, and the suggestive results from interventional studies and observational studies
[119] for preventive effects of high doses on recurrence and occurrence of oral clefts strongly indicate that large doses of folic acid are best suited for evaluation in randomized clinical trials of recurrence.

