This study has the ability to identify, for the first time, the true preventive effects of folic acid on recurrence of oral clefts, using a dose that has proved effective in preventing recurrences of NTDs
[118]. The double blind randomized design will cleanly separate the effect of the intervention from those confounding effects that have plagued previous interventional and observational studies. This study provides the chance to evaluate a treatment that if successful, will determine the standard of care for high risk women in the United States and abroad.

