#### Inclusion and exclusion criteria

##### Inclusion criteria

In this study, NSCL/P is defined as all cases of unilateral or bilateral clefts of the lip with or without cleft palate excluding the following: cases with recognized syndromes, cases with a chromosome abnormality, cases with one or more other major structural anomaly, cases with cognitive delay (IQ or equivalent less than 80), or cases exposed to recognized teratogens in utero (phenytoin or valproic acid). Cases with cleft palate only will not be included in the study as specified in Chapter 1. The following define the inclusion criteria for the study:

1. Women with NSCL/P, who are 16 to 45 years of age (after 45 fecundity decreases substantially) and who attend or have attended the craniofacial clinic for their care.

2. Women (age 16 to 45 years of age) who have at least one natural child of any age with NSCL/P who receives (received) care at the participating craniofacial clinics.

3. All women must reside in the catchment area of the study, which includes the state where the clinic is located and surrounding states.

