##### Exclusion criteria

1. Having a first degree relative (that is a parent, sibling or child) who has cleft palate only.

2. Cases resulting from consanguineous couples (first, second, and third degree, i.e., first cousins or closer).

3. Couples where at least one of the two is definitely sterilized.

4. Women who are using intrauterine devices

5. Women who are using injectible contraceptives

6. Women on anti-epileptic drugs (The metabolism of anti-epileptic drugs requires a great deal of folic acid. Therefore, it is very difficult to verify the effect of folic acid on the prevention of clefting among these women. In order to avoid this situation, such women will not be included in this study).

7. Women on drugs that contain benzodiazepines

8. Women who are pregnant. They will be re-contacted later at an appropriate time for participation in the study.

9. Women who are planning to move outside of the catchment area of the study within the next year.

10. Women who have B12 deficiency (B12 level is below 174 pg/ml or 134.328 pmol/L).

11. Women who are allergic to folic acid.

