#### Blood collection

Folate (Serum and RBC) levels will be assessed, at baseline (prior to supplementation), every 12 months after enrollment, and at pregnancy. B12 levels will be assessed at baseline and subsequently every year to monitor for B12 deficiency. Folate and B12 tests may be conducted at the own laboratory facilities of the clinic/hospital when available or alternatively at local laboratories determined by the Co-Principal Investigator. The Clinical Coordinator and Co- Principal Investigator will monitor B12 levels and will refer subjects with B12 deficiency to the hematology service for treatment. Randomized subjects found to be B12 deficient may be temporarily or permanently suspended from the study drug based upon recommendations of the hematology referral.

Based on clinical and research experience, few subjects (perhaps none) are expected to ask for their blood results. If requested prior to the end of the study, an independent physician serving in the clinic will provide confidential results to the subject. The subject will also have the opportunity to discuss what her results mean (in terms of being within normal range or not) with the physician independently from other study subjects and research unit staff. This procedure will prevent sharing the results with other study participants as well as with any member of the research team. Since no data is available on what these folate measurements will actually mean in terms of the levels of folic acid supplementation that are provided, it would be impossible for any single woman to interpret these data points in a way that could result in her un-blinding. Therefore, any disclosure of folate test results under these specific circumstances will not affect the blinding of study subjects or of research unit personnel.

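### Eligibility and resumption rules make no exception for a pregnancy affected by a neural tube defect, so such a woman can be given blinded 0.4 mg folic acid

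*Protocol article*

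**What the plan says.** On dose, the Abstract refers to "well-documented effectiveness for folic acid in preventing neural tube defect occurrence at 0.4 mg and recurrence with 4 mg". The section on interventional studies of cleft recurrence draws on the same pattern: "The NTD model showing preventive effects of high and low dose folic acid on recurrence and occurrence respectively". The section on objectives and significance describes the trial as "using a dose that has proved effective in preventing recurrences of NTDs".

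On eligibility, the only limit on other malformations sits in the definition of a nonsyndromic cleft under Inclusion criteria, which removes "cases with one or more other major structural anomaly". That describes the index cleft case, not the woman's other pregnancies. None of the eleven Exclusion criteria mentions an NTD. The one family-history exclusion is "Having a first degree relative (that is a parent, sibling or child) who has cleft palate only".

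On what follows a study pregnancy, Follow-up of study subjects says: "Subjects who are willing to resume participation will be assigned to the same treatment group as their previous randomization assignment". The last rows of Table 5 (Schedule B) repeat standard screening and enrolment and keep the original arm.

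**The concern.** A woman with an earlier NTD-affected pregnancy faces a recurrence risk, the setting in which the protocol credits 4 mg. Under the rules as printed she is eligible and has an even chance of 0.4 mg. If an NTD occurs in a study pregnancy and she wishes to continue, she goes back to the same blinded arm. Re-screening does not catch her, because it applies the same criteria.

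At stake is the safety of a few participants and the consistency of the rules with the protocol's own account of the evidence. Bias and power are not at issue.

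**Working it through.** **Inputs from the protocol**
- Women: 5,368 new + 550 already taking part = 5,918 (Sample size).
- Births required: 1,582, so 791 per arm (Power analysis). This figure reproduces: 5% against 2.5%, one-sided 5%, 80% power, with continuity correction gives 792 per arm, 1,584 in total. Exact one-sided Fisher power at 791 per arm is 0.810.
- Births per woman: 1,582 / 5,918 = 0.267. The planned subject-years give 18,897 × 0.0957 / 5,918 = 0.306, which raises the results that use births per woman by about 14%.
- NTD relative risk with 4 mg: 0.28, against groups without folic acid. The text prints a 78% reduction, but 1 − 0.28 = 72%, which is used here.
- NTD baseline: 1 and 5 per 1,000 births, with reductions on 0.4 mg of 16% to 41% and 79% to 85% respectively. These are the Chinese samples; no Brazilian rate is given.

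**Assumptions**
- 0.5 to 1.5 earlier births per woman other than the index child.
- NTD recurrence of 4%, by analogy: the protocol gives about 4% for cleft recurrence in siblings and calls the NTD and cleft recurrence risks near identical.
- For the ceiling only: 0.4 mg gives no protection at all against NTD recurrence.

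**Ceiling per birth**

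0.04 × (1 − 0.28) = 0.0288, or 1 in 35. The floor is zero.

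**Enrolment route**

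| | 1 per 1,000 | 5 per 1,000 |
|---|---|---|
| Women with an NTD history: 5,918 × (0.5 to 1.5) × rate | 3.0 to 8.9 | 14.8 to 44.4 |
| Half allocated 0.4 mg | 1.5 to 4.4 | 7.4 to 22.2 |
| Their births (× 0.267) | 0.40 to 1.19 | 1.98 to 5.93 |
| Preventable NTDs, ceiling (× 0.0288) | 0.011 to 0.034 | 0.057 to 0.171 |

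**Resumption route**
- NTDs expected in the 0.4 mg arm: 791 × 0.001 × (0.59 to 0.84) = 0.47 to 0.66, or 791 × 0.005 × (0.15 to 0.21) = 0.59 to 0.83.
- Chance of at least one: 1 − exp(−0.47) = 0.37 to 1 − exp(−0.83) = 0.56.
- Preventable NTDs, ceiling, if every such woman resumes: (0.47 to 0.83) × 0.267 × 0.0288 = 0.004 to 0.006.

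**Existing safeguards**

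| Section | What it does | NTD in the trial | NTD history before enrolment |
|---|---|---|---|
| Adverse events | Reports serious, unexpected events in fetus or newborn | Makes the case known | No |
| Interim analysis and study monitoring | Data safety monitoring board (DSMB) reviews events by arm | Makes the case known | No |
| Delivery of interventions | Investigator may stop drug after an adverse event | Discretionary; names no alternative dose | No |
| Randomization procedures | "Only a physician attending to the study subject may request revealing the treatment assignment for a clinical purpose" | Possible on request | Possible in principle, but nothing prompts it |

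**The case against.** The strongest reply is that this is an omission in an article that defers to a Manual of Operations. The Protocol violations section refers to that manual for the situations that end enrolment and gives only examples. The manual and the screening form are not shown and may already cover these women. That stands as a limit on confidence. It does not dispose of the point, because the exclusion list is printed as complete and the resumption rule carries no exception.

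The second reply is that there is no contradiction, and this also stands. A reader might infer that the protocol shows 0.4 mg to fail against NTD recurrence. It does not: the 0.28 compares folic acid with none, and women are also expected to get about 300 micrograms a day from fortified flour. That is why the individual benefit is given as a range starting at zero.

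Two further inferences should be resisted:
- The data collection schedule provides for contact after any pregnancy outcome. A reader might take this as requiring return to drug after any outcome, but it governs only contact and asking about willingness.
- A reader might contrast the B12 suspension with the lack of an NTD rule. The B12 text is permissive too, and no firmer than the discretion to stop drug after an adverse event.

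Finally, the expected number of cases is tiny. That is correct, and it sets the severity.

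**Conclusion.** The point holds as a cheap safety improvement of the lowest severity. As printed, the rules allow a woman with a past or in-trial NTD-affected pregnancy to take blinded 0.4 mg, although the protocol credits 4 mg, not 0.4 mg, with preventing NTD recurrence. About 3 to 44 women would have such a history, given 0.5 to 1.5 other births per woman and 1 to 5 NTDs per 1,000. The most that could be prevented across the trial is about 0.17 cases through enrolment and 0.006 through resumption. Both figures assume that 0.4 mg does nothing against recurrence.

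The clearer gap is a history known before enrolment. For an NTD in the trial, existing discretion and monitoring partly help, but nothing says what the woman should take before her next conception. The documents do not support reading this as measurable expected harm, as an absence of safeguards, or as a threat to the primary comparison. Confidence is medium because the Manual of Operations is not shown.

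**What to change.** 1. Add a twelfth exclusion: *Women who have had a pregnancy affected by a neural tube defect (live birth, stillbirth or loss); they are referred for open-label folic acid 4 mg daily after a B12 check.* Ask this at screening and re-screening, and once of women already enrolled, handling any positive answer as in step 2.
2. Add to the resumption sentence and to Table 5: *A subject whose study pregnancy was affected by a neural tube defect does not resume blinded drug. She is referred for open-label folic acid 4 mg daily without unblinding, and stays in outcome follow-up, analysed in her randomised arm.*
3. If the Manual of Operations already has such a rule, state it in these two places instead.

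**Cost**
- New women not enrolled: 5,368 × (0.5 to 1.5) × 0.001 = 2.7 to 8.1, or 13 to 40 at 5 per 1,000. At 0.267 births each, that is 0.7 to 10.8 births, against a margin of (18,897 − 16,531) × 0.0957 = 226. Losing 11 births moves normal-approximation power from 0.8350 to 0.8327.
- Of the 550 already enrolled, 0.3 to 0.8 (1.4 to 4.1 at 5 per 1,000) would move to open-label 4 mg.
- Dilution of the 0.4 mg arm is at most 550 × 1.5 × 0.005 / 2 × 0.267 + 0.83 × 0.267 = 0.77 of 791 births (0.1%). The difference falls from 2.500 to 2.498 percentage points, and power to 0.8345. If the NTD pregnancy was a live birth in the study, the first analysis already leaves out later births. After a loss or stillbirth, her first live birth still counts, so follow-up must continue.
- The results would not cover women with both a cleft history and an NTD history.
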